## Process measures

- Context: Characteristics of cluster (hospital unit): total number of employees, employees participating from cluster, characteristics of employees (age, gender, job position).
- Intervention: module I-V preferences, dose (overall number of sessions, sessions in module I-V), UPSIDES fidelity scale (see 5.3).

# Modules of the complex intervention

The goal of the complex intervention is to improve managing work-related challenges in order to strengthen the well-being (physical and mental health) of hospital employees at different levels of hierarchy and functional areas. The complex intervention is built on experiences from five previous pilot projects carried out between 2017-19. These prior pilots operate on both, the behavioral and the structural levels, and will be used as a combined stress mitigating additive during the complex 10-month intervention period in three locations including clusters from small regional hospitals to university hospitals with full clinical care. A total of five individual modules with different thematic priorities will be offered: (i) Top Management Training, (ii) Promoting Stress preventive relational leadership competence) (iii) Dilemma Competency – Coping by taking responsibility, (iv) Reconciling Work and Family Life and (v) Stay Healthy at work. Importantly and in contrast to other studies, employees may choose one module according to their specific needs and interests depending on their position in the hospital. The maximum duration of one module shall be 12 hours.

## Top Management Training

The purpose of this intervention offered dealing with this subject is to raise awareness and competence among executives regarding the design of health-promoting work and its economic effects. The module to raise awareness includes measures to sensitize management staff on the departmental level (i.e. the leaders of the cluster) for issues of mental health of their employees. Moreover the module includes practical guidance to psychosocial health risk assessment and the development of structures as well as procedures to improve work conditions in the round tables. It is followed by a phase in which participants try to implement the required structures and procedures into occupational practice. The results of the transfer will be discussed in a follow up meeting on a collegial level in order to support further approaches.

## Promoting stress preventive relational leadership competence

Leadership behavior has been described as an important variable in relation to employees` psychological well-being (e.g. Montano et al., 2017). Since the hospital can be perceived as a mental health demanding workplace for employees (e.g., manpower shortage, economical pressure) it is the leader`s responsibility to preserve and foster subordinates` mental health. Therefore, we provide a leadership intervention which concentrates on relational and stress preventive aspects of leadership. It is open for middle management of all occupational groups at hospital and consists of four modules with a total duration of twelve hours. Between two modules a practice phase during which participants implement their new knowledge and techniques into their situation at work is conducted. Every module comprises theoretical parts (e.g., theoretical input through frontal presentations, instructional videos) to generate new knowledge as well as practical and interactive parts (e.g., group discussions, role pays, single work or partner work) to discuss and transfer this knowledge into the everyday work. Concerning the content the modules focus on a) a competent handling of leaders` stress as a requirement for leading, b) health and relational oriented leadership behavior like transformational leadership (Podsakoff et al., 1990) and Leader – Member-Exchange (LMX; Graen & Uhl-Bien, 1995) to provide successful working relations, c) motives, needs and stressors of subordinates to foster a mindful communication and d) managing team meetings and understanding team dynamics to lead teams stress preventive.

## Dilemma Competency – Coping by taking responsibility

For this intervention, an already successfully implemented training (Zwack & Bossmann, 2017) on dilemma competency to meet the working conditions in the public health sector has been adapted. Each group intervention consists of 2 days of 6 hours each and is administered over a period of 2 months.

The aim of the intervention is to provide the participants with mental and action-related abilities to understand contradictory demands in their organization and to meet associated demands constructively through negotiation and decision-making processes.

Overall the element of the complex intervention strives for prevention of stress-related diseases and the promotion of an enhanced sense of meaningfulness experienced by the participants. In times of an increasing aggravation of working conditions due to economic strain, competitive constraints and shortage of skilled employees in the health care system, dilemma management supports employees in dealing with daily work strains.

## Reconciling Work and Family Life

The one-day module lasts six hours (four modules 90 minutes each) and the maximum number of participants is 15. Aim of the module is to improve one's ability to cope with reconcilability stress by enabling a personal analysis and reflection of each participant's situation. This analysis of the professional and family environment is guided by worksheets specifically developed for the intervention, which are worked on individually or in groups. Further central elements are the subject-related impulse lectures regarding the connection between stress experience, stress response and the influence of personal stress on the relationship to the child as well as developmental psychological findings for practical everyday life as a parent. The participants are also instructed on practical stress management in the form of yoga. In contrast to a pure coping workshop, this module is also highlighting the constellation "dilemma" in the context of a role-play, in order to work out how to deal with an unsatisfactorily solvable compatibility situation in a further step.

## Stay Healthy at Work

In a small group intervention with up to 15 participants on two days the topics age and getting older at work, reflection on one's professional biography and defining resources, dealing with stressors, Selection, Optimization and Compensation (SOC) concept, personal processing of an individual project within the SOC framework, physical health and work-life balance will be dealt with. The participants will be informed about various coping strategies such as: relaxation exercises/techniques (autogenous training, fantasy trips, PMR) and mindfulness exercises.

## Roundtable discussions and booster sessions

In addition to the modules, roundtable discussions were offered to facilitate organizational change and develop concrete proposals for action. Due to the small number of participants, the following adjustments were made to the round tables: Instead of one round table per module type, one round table together with one booster session were offered for all module types at each study location. Booster sessions were offered to enhance training effects. In these booster sessions the exchange of transfer experiences from training into daily hospital life is enabled. It is hoped that some participants will continue to exchange experiences in a self-organizing fashion, even after project termination. The duration for booster sessions and 1^st^ order round tables is 3-4 hours.

The Round Tables are a participation instrument in which representatives of different positions and interests come together under a neutral moderation in order to process various suggestions for improvement made by employees during the modules. As a first step, concrete measures operating on the structural level will be developed (so-called 1^st^-order round tables), which will be presented in a second step to the decision-makers at each study location (including the Executive Board; so-called 2^nd^-order round tables). The duration of the 2^nd^-order round tables is 3-4 hours.

# Design of the Trial

## Trial Design

The study is designed as a multi-centre cluster-randomized open trial with a waitlist control group.

## Randomisation and Blinding

For organizational reasons, cluster-randomization will be carried out prior to recruitment of the first participants. The allocation will be done stratified by the three locations in a 1:1 fashion using a randomization list which will be prepared by the Institute of Medical Biometry and Informatics. If appropriate, cluster pairs per site will be defined in order to prevent that matched pairs will be randomized into the same group. Due to the nature of the intervention blocks, blinding of participants and trainers is not possible.

## Additional Methods for Reducing Bias

Participants will be given access to a separate room to fill out the questionnaires.

## Duration of Trial Period(s)

Total trial duration is 12 months, consisting of a 10-month intervention phase. The different intervention modules vary in their duration: The first intervention module – Top Management Training– has a duration of one working day, the Promoting stress preventive relational leadership competence has a total duration of 3 weeks. The third intervention module – Dilemma Competency – Coping by taking responsibility – will be administered over a period of 2 months. The intervention module Reconciling Work and Family Life has a duration of one working day while Stay Healthy at Work is offered over a period of 4 weeks. Booster sessions and the 1^st^-order round tables will take place at the beginning of October 2020, the 2^nd^-order round tables will be held at the end of October, before T2*.

# Study population and withdrawal of subjects

## Number of Subjects

All employees in the participating units of the three study locations (Aalen/Ellwangen, Heidelberg, Duisburg) will be potential participants. At least six clusters are planned per location, with altogether in about 720 potential participants (360 participants in intervention and 360 participants in waitlist control group).

## Subject Inclusion Criteria

Inclusion criteria for study locations are:

- Willingness to participate in the study regardless of randomization to the intervention or waitlist control arm
- Willingness to complete three questionnaires (applicable to intervention group, waitlist control group and cluster participants)

Eligible criteria for employees who want to take part in one or more interventions are:

1. Age: 18-70 years old,
2. Written informed consent,
3. Sufficient German language skills to fill out the questionnaires

## Subject Exclusion Criteria

Exclusion is limited to the negotiation of the inclusion criteria.

## Subject Withdrawal Criteria

All participants are informed that they can terminate their participation in the study at any time without stating reasons.

# Study process

Eligible clusters will be identified in three study locations (Aalen/Ellwangen, Heidelberg, Duisburg). Interested employees in these clusters will be informed about the study and the different interventions by means of information events or by the operational health management of the respective location. Verbal and written information will be given to all employees interested in the interventions. The study staff will contact potential participants and obtain written informed consent. A choice of five modules will be offered to the study participants with the restrictions mentioned above. For participants in clusters randomized into the intervention group, the remaining modules will start within the intervention phase. For participants in clusters randomized into the waitlist control group, the five modules will begin after the intervention phase. As a possible disadvantage, the participants in the waitlist control group might feel deterred by the long waiting time of 12 months.

# Safety

The collected data will comprise of self-reported questionnaires, personal interviews and process produces data e.g. from modules. The intervention and control group will not undergo any invasive or potentially harmful procedure, therefore no adverse events or safety parameter definition is necessary.

# Data Collection, Data Management and Archiving

## Data collection

Individual participant data (demographics and questionnaires on individual level) will be collected at T0, T1* and T2* (starting end of 2019) either paper based (CRF) or web based electronically (eCRF) in order to meet individual preferences.

Organisational indicators (on hospital/clinic level, assigned to clusters) will be collected either paper based or electronically as well. Paper based questionnaires will be sent to the IMBI by post. Data will be captured via double data entry near term to receipt and it will be transferred to a statistical analysis system running on a server located in the IMBI subsequently to data capture.

Data captured in the eCRF will be transferred to the analysis system as well. The electronic data capture system (EDC-system) underlying the eCRF is also running on a server located in the IMBI. Data related to process evaluation will be collected and stored separately.

## Data Management

The system used for web based electronic data capture (EDC-system) is validated and compliant with FDA 21 CRF part 11. Data transmission is encrypted with secure socket layer (SSL) technology. The database server in the IMBI is located in a secure data centre and protected by a firewall. The system provides an infrastructure to support user roles and rights.

Only authorized users are able to enter or edit data. The access to centre specific organisational data is restricted to persons of the respective centre. Access to individual data is restricted to the participant only. All changes to data are logged with a computerized timestamp in an audit trail within the EDC-system.

Any modification of data captured from paper based questionnaires via double data entry (e.g. as result of queries) will be logged within the analysis system as well.

All individual data will be captured, transferred and stored in a pseudonymized manner.

Backups of both, EDC-system and the statistical analysis system are conducted regularly.

High quality of data will be guaranteed by checking for completeness, consistency and plausibility on or near term to data entry. This will be realized by implementation of programed validation rules, predefined in a data validation plan. The validation programs will generate queries/edit checks on data entry within the EDC-System and/or subsequent to data transfer to the analysis system by generating paper based queries. The investigators or the designated representatives are obliged to clarify or explain the edit-checks and queries.

During study conduct, the database is accessible to the data manager and data entry staff only. After database closure, access rights will be granted to the responsible biometricians as well.

Data will be managed and analysed according to the corresponding Standard Operating Procedures (SOPs) valid in the IMBI.

Business data will be transferred to the Chair of Business Administration, esp. Organization and Human Resources of the Heinrich-Heine-University Düsseldorf for analyses.

## Archiving

Study data and study documents stored in the IMBI will be transferred to the study coordinator subsequent to statistical report and/or publication for archiving.

# Statistics

## Sample Size Calculation

The sample size calculation is based on the primary endpoint, i.e. the absolute change in the total score of the IRR from T0 to T2*, which will be evaluated by an ANCOVA approach. The sample size is calculated based on a two-sided two sample t-test with two-sided significance level α = 0.05 and power 1-β = 0.8, which provides a conservative estimate for the necessary sample size for the ANCOVA evaluation. The intervention is assumed to yield a medium effect, hence an effect size of d = 0.4 is used for sample size calculation. These assumptions yield a sample size of 100 participants per group (200 for both intervention and control). Taking into account the dependencies within clusters and simultaneously being conservative via assuming a high intraclass correlation coefficient of ICC = 0.05 and a mean cluster size of about 40 participants yields a design effect of 1 + 0.05*(40-1) = 2.95. Therefore, the necessary sample size is 2.95*200 $\approx$ 590 participants. Furthermore, a drop-out rate of 18% will be considered. Taken together, this amounts to a total sample size of 720 participants in 18 clusters. Under consideration of possible cluster drop-outs, more than 18 clusters might be recruited which will lead to an increased power. The sample size was calculated using the software SAS 9.4.

## Statistical Methods

The primary analysis tests the null hypothesis that the absolute change in the total score of the IRR from T0 to T2* in the intervention group is equal to the absolute change in the total score in the control group. The analysis of the primary endpoint will be based on an ANCOVA model comparing the treatment groups including the baseline value of the total score of the IRR at T0 (baseline) with the total score of the IRR at T2* (11 months after T0; follow-up) between intervention and control group, including hierarchy level (top management, middle management and employees without management responsibility) and gender (female, male) as well as the site (planned are three) as covariates and the respective cluster as random effect. In case of significance, the WHO-5 will be tested in hierarchical manner in the same way. Again, in case of significance, the PSC-12 will be tested. Applying this hierarchical testing strategy the overall type I error will be controlled. All other analyses will be of exploratory nature and interpreted only in descriptive manner. The primary analysis will be conducted based on the full analysis set reflecting the intention to treat principle including all participants in the group the respective cluster was randomized to. As sensitivity analyses, the per-protocol population (only participants which fulfil the inclusion criteria) will be analysed. There, only participants of the intervention group who participated in at least one session of a module are considered in the intervention group. Otherwise, these participants will be excluded from the analysis. The participation of individuals from the intervention group in further programs (round tables and booster sessions) will be considered as additional covariate in further analyses of primary and secondary endpoints.

The analysis of the secondary endpoints within the population of cluster participants will be based on an ANCOVA model as well, comparing the cluster participants including the baseline value of the total score of the IRR, WHO-5, PSC-12 or single items at T0, respectively, with the total score of the IRR, WHO-5, PSC-12 or single items at T2*, respectively, between cluster participants of a cluster randomized into intervention group and cluster participants of a cluster randomized into control group, including hierarchy level (top management, middle management, employees without management responsibility) and gender (female, male) as well as the site (planned are three) as covariates and the respective cluster as random effect. As additional secondary analyses, changes in the collected scores from T0 to T1* will be analysed.

All data of clusters and participants will be described by treatment group. Categorical data will be presented as frequencies and percentages. For continuous data, the number, mean, standard deviation, median, inter-quartile range, minimum and maximum will be calculated.

For further evaluation of potential factors influencing treatment effect, moderator and mediation analyses as well as subgroup analyses will be conducted. As example, the subgroup of a specific level of hierarchy will be evaluated. A detailed description of the planned statistical analyses will be provided in the Statistical Analysis Plan (SAP) which will be finalized prior to database closure and any analysis. All analyses will be conducted using SAS 9.4 or higher.

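### Round-table and booster attendance, defined only in the intervention arm, should not be a covariate in models that compare the arms

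*Protocol*

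**What the plan says.** Section 13.2 of the protocol makes the full analysis set, as randomised by cluster, the basis of the primary ANCOVA and of the hierarchical tests of WHO-5 and PSC-12. Everything else is exploratory and to be read descriptively. The same section then fixes two further analyses.

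- **Attendance covariate.** Participation of intervention-group individuals in round tables and booster sessions "will be considered as additional covariate in further analyses of primary and secondary endpoints".
- **Per-protocol set**, planned as a sensitivity analysis. In it, "only participants of the intervention group who participated in at least one session of a module are considered in the intervention group". The text continues: "Otherwise, these participants will be excluded from the analysis". No attendance condition is set for the waitlist arm.

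Other sections supply the context. Clusters are randomised before recruitment (8.2). Booster sessions and round tables take place in October 2020, before T2* (8.4). Boosters are meant to strengthen the training effect, and round tables to bring about organisational change (7.6). Waitlist participants start their modules only after the intervention phase (10).

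**The concern.** A covariate in a randomised comparison should be fixed before treatment starts, or at least be unaffected by it. Round-table and booster attendance is neither: it is a component of the intervention, taken up by some participants after allocation, and it has no defined counterpart among controls. Adjusting for it changes what the arm coefficient measures.

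The per-protocol rule has a related weakness. It removes intervention participants who attended no module session but keeps the controls who would not have attended either.

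What is at stake is interpretation. A reader who sees an attendance-adjusted arm effect, or a per-protocol effect labelled as a sensitivity analysis, will tend to set it beside the intention-to-treat result as support or contradiction. Neither can serve that purpose unless attendance is unrelated to prognosis.

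**Working it through.** **The plan's own figure.** Section 13.1 uses "two-sided significance level α = 0.05 and power 1-β = 0.8" and "an effect size of d = 0.4 is used for sample size calculation". A two-sample t-test then needs 99.08 per group, rounded up to 100, as stated. With the stated design effect, 2.95 x 200 = 590. With 18% drop-out, 590 / 0.82 = 719.5, so 720, and 720 / 40 = 18 clusters. The figure is reproduced and this point does not change it. Here d = 0.4 serves only as a yardstick.

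**What the adjusted model estimates.** Count improvement as positive. Let A = 1 for an intervention participant who attended a round table or booster and A = 0 otherwise, so that A = 0 for every control. Let p be the share attending in the intervention arm. Holding the other covariates fixed:

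- attendance coefficient = mean(intervention, A = 1) - mean(intervention, A = 0)
- arm coefficient = mean(intervention, A = 0) - mean(control)
- ITT effect = p x mean(intervention, A = 1) + (1 - p) x mean(intervention, A = 0) - mean(control)

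Hence arm coefficient = ITT - p x (attendance coefficient).

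The attendance coefficient has two parts: delta, the difference in prognosis between attenders and non-attenders, and tau, any true effect of the sessions. The arm coefficient therefore misses the ITT effect by p x (delta + tau). The part p x tau is real benefit taken out of the treatment effect; the part p x delta is selection.

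**Size of the selection part.** The protocol gives neither p nor delta, so both are assumed:

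| p | delta (SD) | p x delta (SD) | as share of d = 0.4 |
|---|---|---|---|
| 0.1 | 0.3 | 0.03 | 7.5% |
| 0.3 | 0.3 | 0.09 | 22.5% |
| 0.5 | 0.5 | 0.25 | 62.5% |

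**Per-protocol set.** If a share e of the intervention arm is excluded and delta is now the prognostic difference between module attenders and non-attenders, the selection part is e x delta. At an assumed e = 0.2 and delta = 0.3 SD this is 0.06 SD, or 15% of 0.4.

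**Simulation check.** The set-up was 18 clusters of 33 (720 x 0.82 / 18 = 32.8), ICC 0.05 and ANCOVA on baseline, fitted by least squares for point estimates only. An unmeasured engagement trait improved the outcome by 0, 0.2 or 0.4 SD per SD and correlated 0.7 with attendance. Between 50% and 90% attended a module, 20% to 50% attended a round table or booster, and the round tables and boosters themselves had no effect.

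| Estimate when engagement matters (0.2 or 0.4) | True effect 0 | True effect 0.4 |
|---|---|---|
| ITT | about 0 | about 0.40 |
| Arm coefficient adjusted for attendance | -0.04 to -0.22 | 0.17 to 0.35 |
| Per-protocol | +0.03 to +0.22 | 0.43 to 0.62 |

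With a true effect of 0, the attendance coefficient was +0.22 to +0.49 SD although the sessions did nothing. When engagement was unrelated to outcome, the ITT, adjusted arm and per-protocol estimates agreed.

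Two features of this set-up matter. Engagement was independent of baseline, so baseline adjustment removed none of the selection; in the trial, baseline IRR, hierarchy level, gender and site may remove some. Engaged participants were also assumed to do better; if the more strained staff attend, the signs reverse.

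**The case against.** The strongest reply is that nothing confirmatory depends on these analyses. That is correct. A reader might infer that the randomised comparison of the primary endpoint, WHO-5 or PSC-12 is compromised; it is not, because those tests use the full analysis set and section 13.2 already labels the rest exploratory and descriptive. The label does not, however, say what the coefficients estimate.

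Secondly, section 13.2 does not write out the covariate model. An adherence model within the intervention arm would fit the wording, and sections 5.3 and 6.3 plan process analyses of fidelity and dose. This stands, so the point is limited to models containing both arms. But the sentence applies to further analyses of the primary and secondary endpoints, which are defined as differences between arms, so the two-arm reading is the natural one and should be ruled out.

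Thirdly, an attendance rule can only be applied to the arm that has sessions, and a per-protocol analysis beside a primary ITT analysis is conventional. This also stands. The one-sided set is not an error in itself; only its use as a robustness check is unsafe.

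Fourthly, large biases are doubtful. Section 7.6 reports few participants, with one round table and one booster session per location. Against 360 planned intervention participants, about 120 per location if equal, p = 0.5 would mean about 60 people at each. A reader might take the 0.25 SD row as an estimate, and the protocol does not support that. Nor does it settle p, since a small number of participants could also mean a smaller intervention arm.

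Finally, the protocol does not say that attendance is purely self-chosen (round tables bring together representatives of different groups), nor does it expressly bar waitlist staff. The argument needs neither: it rests on the covariate being defined for the intervention group only.

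**Conclusion.** The point holds for any model that contains both arms. With the planned covariate, the arm coefficient is a contrast of intervention non-attenders with all controls, and the attendance coefficient is a non-randomised comparison within one arm. This follows from the definition of the covariate and needs no assumed figures.

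The size does rest on assumptions: 0.03 SD at p = 0.1 and 0.09 SD at p = 0.3, both with delta = 0.3 SD, plus the loss of any true effect of the sessions. Direction depends on who attends.

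It would go too far to say that these analyses estimate no treatment effect at all. They fail to estimate the randomised effect unless attendance is unrelated to prognosis and, for the adjusted model, the sessions themselves have no effect. The ITT analyses, the hierarchical tests and the sample size are unaffected, so this is a correction to supporting analyses and does not threaten the trial's main conclusion.

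**What to change.** 1. In section 13.2, and in the SAP where it carries this over, remove round-table and booster attendance from every model that compares the arms.
2. Report outcomes by round-table or booster attendance within the intervention arm only, labelled descriptive and non-causal.
3. Keep the per-protocol set if wanted, but describe its result as a non-randomised comparison and do not offer it as evidence that the ITT effect is robust.
4. A complier-average estimate, with randomised arm as instrument and at least one module session as exposure, is optional. It requires that allocation has no effect on participants who attend nothing. The trial itself looks for such an effect: staff who take no module are surveyed for dispersal and organisation-level influence (Protocol Summary, 5.2), cluster leaders are trained (7.1), and round tables aim at organisational change (7.6). The assumption should be stated together with that reason to doubt it. For this reason the estimate is not a straightforward replacement.

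The cost of items 1 to 3 is a change of wording, and no attendance-adjusted treatment effect will be reported. Item 4 adds one model with a wider interval.
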